**Fig. 1 Fig1:**
[figure not shown]
Graphical display of the delayed-start design

#### Treatment at phase 1

During the active treatment phase, all participants will receive 5 Hz aTMS over the L DLPFC, 4 treatment sessions a day (each session consisting of 3000 pulses for 12 000 pulses a day), every weekday for 1 week. We will use a Magventure X100 TMS Therapy System to conduct TMS stimulation. The first treatment session will take approximately 3 h as participants will also be familiarized with the TMS equipment/procedure and resting motor threshold (RMT) will be determined at this session. We use visual assessment of the respective dorsal interosseous muscle contraction (5 out of 10 stimulations) induced by TMS to determine RMT. Subsequent sessions are expected to last about 2 h each. Stimulation will be applied at the left prefrontal cortex (F3 according to the EEG 10/20 system). L DLPFC aTMS will be delivered at 120% of the RMT, as measured at the initial session. Each TMS train will last for 8 s and have a 12-s intertrain interval. Each session will have 75 trains. Thus, it will be taking about 25 min for each session which includes setting up time.

aTMS will be conducted in a room with facilities for managing seizures. Participants and experimenters will be offered earplugs during the sessions. Sessions will be done by staff trained and credentialed in TMS according to the Singapore College of Psychiatrists guidelines for TMS. Staff will also be trained for initial seizure management.

Patients in the delayed-start group will be treated as usual during the delayed week and will receive aTMS treatment at 1 week after recruitment. Subjects in the delayed-start group and early-start group will both be monitored with weekly outcome assessments. Subjects in the delayed start arm who still fulfill the criteria for study entry at the end of the delayed start phase will continue on to the active treatment phase of the study. No change in psychiatric medication will be allowed during this period.

#### Evaluation of clinical response at phase 1

A blinded, the trained rater will assess mood each week, from baseline to 2 weeks after treatment, using the Montgomery-Asberg Depression Rating Scale (MADRS) scale. MADRS scale is more sensitive to change in patients’ mental condition than Hamilton depression rating scale [44]. The primary outcome is response rate, which are assessed at end of week 4 and week 6. Secondary outcomes include remission rate, Clinician Global Impression –Improvement Scale (CGI-I) and the self-rated Quick Inventory of Depression (QIDS-16). Patient’s cognition will be monitored using the Montreal Cognitive Assessment Scale (MoCA) before and after the 1-week active treatment period and quality of life (QoL) measured by the Quality of Life Enjoyment and Satisfaction Questionnaire – Short Form (*Q*-*LES*-*Q*-SF), assessed at baseline and end of week 2. MoCA is a brief cognitive instrument recommended for screening for cognitive impairment (CI) in patients. Several studies have compared the discriminant abilities of the MoCA and the Mini-Mental State Examination (MMSE) for screening post-stroke CI, and most studies have demonstrated that the MoCA is superior or equivalent to the MMSE for the detection of CI after stroke. Furthermore, the MoCA has been reported to be sensitive to changes in acute temporary CI after mild stroke/TIA, whereas the MMSE is reportedly not [45]. Therefore, in the current study, we use MoCA to assess acute changes in cognitive abilities.

After aTMS treatment, all subjects will then be followed up once a week for 2 weeks and subjects who achieve remission will exit the study.

#### Randomization at phase 2

Subjects who have not remitted from the 1st active treatment will enter phase 2 treatment. The second randomization will be stratified into three groups based on whether the participant showed <25% improvement in MADRS scores, between 25% and ≤50% improvement in MADRS scores or >50% improvement in MADRS scores. After that, participants in each group will be randomized (in permuted blocks) to either L DLPFC or R DLPFC treatment. The purpose of patient stratification basing on MADRS score before randomization is a method of permuted block randomization, which is a way to randomly allocate a participant to a treatment group, while maintaining a balance across treatment groups. Each “block” has a specified number of randomly ordered treatment assignments depending on the response to the initial aTMS treatment. Randomization will be generated by study team members who are not involved in the treatment. Treatment assignment is determined by treating doctors. Patients, their caregivers, nurse clinicians, and doctors who do the treatment and outcome assessments will be blinded to the randomization.

#### Treatment at phase 2

Subjects who entered phase 2 will receive another 1 week of 5 Hz L DLPFC aTMS (same protocol as above) or aTMS consisting of right DLPFC at 1Hz, 4 treatment sessions a day (each session consisting of 3000 pulses for 12000 pulses a day), every weekday for 1 week. These patients will also be followed up with weekly assessments for 2 weeks after the end of the second round of aTMS. Therefore, participants who receive a total of 1 week of daily aTMS would have received 60000 pulses while those who received a total of 2 weeks of daily aTMS would have received 120000 pulses.

We will use the Magventure X100 to carry out low-frequency R DLPFC. 1 Hz R DLPFC aTMS will take about 4 h a day. Stimulation will be delivered at the right prefrontal cortex (F4 according to the EEG 10/20 system). R DLPFC aTMS will be delivered at 120% of the RMT, as measured at the initial session. Each session will have 300 trains which is equivalent to a consensus protocol of delivering 3000 pulses per session over the L DLPFC [46].

#### Evaluation of clinical response at phase 2

Similar to the outcome assessment during phase 1, mood improvement and subject QoL will be assessed every week during acute treatment by a trained rater (blinded to treatment allocation) using the MADRS scale until 2 weeks after the initiation of 2nd round of treatment.

In summary, the primary outcome of this study will be a mean change in the MADRS score from baseline to the end of 4 weeks after treatment initiation. The primary endpoint of the trial will be the MADRS score <11 at any time points of follow-up after initiation of rTMS treatment which indicates the patients have achieved symptoms remission hence can exit from the study.

See Fig. 2 for the flowchart of the study design.

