## Methods

### Objectives

The primary aim of this study is to test the symptomatic efficacy of aTMS trial protocol. The 2nd aim is to compare the symptomatic efficacy of the early-start aTMS treatment group and delayed-start aTMS treatment group in patients with a DSM 5 Major Depressive Episode. The exploratory aim is to test whether the non-responders to a 1-week course of aTMS will have a higher chance of response to a change in aTMS than repeated the same aTMS modality (from 5 Hz L DLPFC aTMS to 1 Hz R DLPFC aTMS).

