#### Inclusion criteria

Age ≥21 years.DSM-5 diagnosis of current major depressive disorder.Montgomery-Asberg Depression Rating Scale score of 20 or more.Able to give informed consent.

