#### Exclusion criteria

DSM-5 psychotic disorder.Drug or alcohol abuse or dependence (preceding 3 months).Inadequate response to ECT (current episode of depression).Rapid clinical response required, e.g., high suicide risk.Significant neurological disorder, which may pose increased risks with TMS, e.g., epilepsy.Metal in the cranium, skull defects, pacemaker, cochlear implant, medication pump, or other electronic devices.Pregnancy.

The following clinical data will be collected at baseline: age, gender, ethnicity, duration of index episode, type of depression (unipolar/bipolar, melancholic/non-melancholic), number of failed antidepressant treatments, number of previous depressive episodes, age at the first depressive episode, and family history of affective disorder will be noted. Full informed written consent will be obtained from all participants.

#### Randomization at phase 1

In phase 1, subjects were randomly assigned either to the early-start group (immediate active treatment) or the delayed-start group (no TMS treatment for one week followed by active treatment, see Fig. 1). Randomization was done using a random sequence number generator.

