
### Sample size calculation

Based on our center’s TMS results to date, patients start TMS treatment with an average MADRS score of 25.4 (SD 7.3), which decreases significantly to 18.4 (SD 9.9) after 2 weeks of treatment with standard rTMS and to 14.1 (SD 10.7) after 4 weeks of treatment. Participants enrolled in the study would be expected to have similar improvements in MADRS with aTMS treatment.

This study is powered to test the primary aim, i.e., a significant reduction in MADRS scores from baseline to end week 3, in the overall study sample. Based on the MADRS scores cited above for baseline (25.4 ± 7.3) and end week 4 (14.1 ± 10.7) time points, detecting a similar significant change after a course of aTMS would require a sample of 12 participants (alpha 0.5, 95% power). However, given the lack of data on the efficacy of aTMS in an Asian population, and to give a better estimate of response and remission rates, we anticipated that 60% of those recruited will drop out before the end of the trial with an unequal allocation ratio of 2:1, we thus aim to recruit 40 subjects in the delayed start arm and 20 subjects in the immediate start arm for a total of 60 subjects.

No prior data exist on the comparative effects of delayed response with immediate treatment of aTMS (or TMS), we will also explore the aim that non-responders to a 1-week course of aTMS will have a higher chance of response to a change in aTMS from L 5 Hz DLPFC TMS to R 1 Hz DLPFC for depression. This study will produce pilot data for 2nd and exploratory aim, informing the power analysis for a future clinical trial if results reject a null hypothesis.

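### Only the delayed arm must re-meet the entry criteria after randomisation, so the second-aim comparison of treated groups sets a selected subset against an unselected arm

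*Protocol article*

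**What the plan says.** All references are to the Protocol article.

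- **Entry.** Inclusion criteria require a "Montgomery-Asberg Depression Rating Scale score of 20 or more".
- **Early arm.** Randomization at phase 1 gives this arm active treatment immediately. No second eligibility check is described.
- **Delayed arm.** Under Treatment at phase 1, these patients have usual care for a week and "will receive aTMS treatment at 1 week after recruitment". That step is conditional: "Subjects in the delayed start arm who still fulfill the criteria for study entry at the end of the delayed start phase will continue" to active treatment. Both arms have weekly outcome ratings.
- **Comparison affected.** Objectives: "The 2nd aim is to compare the symptomatic efficacy of the early-start aTMS treatment group and delayed-start aTMS treatment group". Sample size calculation describes the data for this aim as pilot.
- **Primary test.** Sample size calculation powers the trial for "a significant reduction in MADRS scores from baseline to end week 3, in the overall study sample". This is a pre-post change with the arms pooled.
- **Timing.** Evaluation of clinical response at phase 1 runs MADRS ratings from baseline to two weeks after treatment, has quality of life "assessed at baseline and end of week 2", and places MoCA before and after the treatment week. It also names weeks 4 and 6 for response. Evaluation of clinical response at phase 2 counts four weeks from treatment initiation.

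**The concern.** A patient who improves below MADRS 20 in the first week is handled differently by arm. In the early arm that patient has already started aTMS and stays in the treated group. In the delayed arm the same patient does not go on to aTMS and never joins the treated group. The re-check comes after randomisation, uses the scale on which efficacy is judged, and acts in the larger arm (40 of 60).

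Aim 2 is worded as a comparison of aTMS treatment groups. Read that way, it sets all early patients against only those delayed patients who did not improve enough to be screened out, and randomisation no longer protects the contrast. The selection also removes the very patients who show what a week without aTMS does.

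A second, smaller matter is the clock. The arms start treatment a week apart, and the article does not tie the end of week 3 (MADRS) or the end of week 2 (quality of life) to one starting point for both arms.

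**Working it through.** **1. The plan's own figure.** The article gives no figure for the share failing the re-check. Its one sample-size figure, 12, is for the pooled test. With SD of change = sqrt(7.3² + 10.7² - 2 × 0.5 × 7.3 × 10.7) = sqrt(89.67) = 9.47 (correlation 0.5 assumed), a difference of 25.4 - 14.1 = 11.3, two-sided alpha 0.05 and 95% power, a paired t-test needs 12. (Alpha is printed as 0.5; at that value 12 is not reproduced.) This is a one-sample calculation, so the re-check does not alter it.

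**2. Inputs for the selection.** From the article: mean 25.4, SD 7.3 (Sample size calculation), cut-off 20, delayed arm 40. Assumed: normal scores, 25.4 taken as the mean before the entry cut, one-week correlation r of 0.6 to 0.9, and a true waiting-week change of 0 or -2 points.

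**3. Entry cut by formula.** z = (20 - 25.4)/7.3 = -0.74, so 77% qualify. Mean of those who qualify = 25.4 + 7.3 × 0.303/0.770, about 28.3, which is 2.88 above 25.4. With no true change, the expected waiting-week change in the whole delayed arm is -(1 - r) × 2.88: -1.15 at r = 0.6 and -0.29 at r = 0.9.

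**4. Second cut by simulation (2 million draws).** The third results column is the randomisation MADRS of retained patients minus that of all randomised.

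| r | True change | Fail re-check | Of 40 | Retained minus all | Week change, whole delayed arm | Week change, retained |
|---|---|---|---|---|---|---|
| 0.6 | 0 | 14.3% | 5.7 | 0.58 | -1.16 | -0.01 |
| 0.7 | 0 | 12.3% | 4.9 | 0.59 | -0.87 | -0.01 |
| 0.8 | 0 | 10.1% | 4.0 | 0.57 | -0.57 | 0.00 |
| 0.9 | 0 | 7.1% | 2.8 | 0.46 | -0.29 | 0.00 |
| 0.6 | -2 | 22.4% | 8.9 | 0.90 | -3.16 | -1.51 |
| 0.7 | -2 | 20.2% | 8.1 | 0.96 | -2.86 | -1.59 |
| 0.8 | -2 | 17.9% | 7.1 | 0.99 | -2.58 | -1.69 |
| 0.9 | -2 | 15.0% | 6.0 | 0.98 | -2.29 | -1.80 |

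The simulated whole-arm changes agree with step 3. The zero in retained patients is expected: with no true change, two scores that must both reach 20 are interchangeable, so their mean difference is zero. The improvement sits in those removed. At r = 0.6 they changed by -8.06, and 0.143 × (-8.06) = -1.15.

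**5. Calendar.** Early arm: treatment in week 1, follow-up in weeks 2 and 3. Delayed arm: wait in week 1, treatment in week 2, follow-up in weeks 3 and 4.

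| Visit | Origin | Early: weeks since treatment ended | Delayed |
|---|---|---|---|
| End of week 3 | Recruitment | 2 | 1 |
| End of week 2 (quality of life) | Recruitment | 1 | 0 |
| End of week 3 | First session | 2 | 2 |
| End of week 2 (quality of life) | First session | 1 | 1 |

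**The case against.** **Nothing says that non-requalifiers leave the analysis.** Analysis sets belong in the full protocol or SAP, and weekly ratings are promised in both arms. This is fair: an as-treated analysis is inferred from the wording of the aim. But the one-sided re-check is explicit, the aim names treatment groups, and ratings end two weeks after treatment, which gives an untreated patient no end point. An SAP cannot recover ratings that were not scheduled.

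**The wait is intended to curb placebo response.** Strengths and limitations says so. Screening out early improvers would serve that purpose in a lead-in common to both arms. Applied to one arm only, it unbalances the comparison.

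**The effect is small and the aim is pilot.** A shift of 0.5 to 1.0 points is small beside the 11.3-point change used for sizing, and aim 2 is not powered. Both points stand and limit the severity.

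**Stronger readings a reader might infer, which the article does not support:**

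- *Baseline and week 3 do differ by arm.* No section counts weeks from enrolment, and several anchors are to treatment. One treatment week plus two follow-up weeks is exactly the end of week 3 on a treatment clock. The design figures are not shown. Only the lack of a stated common origin can be claimed.
- *The primary test is invalidated.* It is a pooled pre-post change, so there is no randomised comparison for the re-check to break. Its lack of a sham control is acknowledged in the article.
- *A re-qualified baseline must add regression to the mean.* With no true change, the simulated later drift is -0.18 to -0.86 from the post-wait score in retained delayed patients, against -0.29 to -1.15 from the randomisation score in the early arm. It is smaller here, and it depends on the assumed correlation structure.
- *More patients fail even with no true change.* That needs a lower starting mean than 25.4, and the article gives none.

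**Conclusion.** The point holds for aim 2. A comparison of the treated groups would use a delayed group selected after randomisation on the outcome scale, against an early group with no such selection.

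About 3 to 6 of 40 delayed patients would be removed with no true change, and 6 to 9 of 40 with a true 2-point fall. The shift in randomisation MADRS is modest. The more telling loss is that, with no true change, retained patients show about zero waiting-week change while the whole delayed arm shows -0.3 to -1.2. The untreated improvement that the delay could reveal is hidden.

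These sizes rest on normality, on 25.4 as the mean before the entry cut, and on assumed correlations and waiting-week change. The direction of the selection does not rest on them. The timing point is conditional: a one-week difference in time since treatment arises only if weeks are counted from recruitment. This should be corrected, but it does not undermine the powered aim.

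**What to change.** Leave the rule on who is treated as it is, and change the analysis and follow-up wording.

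1. **Aim 2.** Compare early with delayed start in all randomised patients at the end of week 1, before the re-check acts. The weekly MADRS already scheduled supplies the data, and the re-check itself needs that rating in the delayed arm.
2. **Non-requalifiers.** Keep them in weekly MADRS follow-up with a stated end point, analyse them in their randomised arm, and report their number.
3. **Pooled pre-post test.** Define baseline as the last MADRS before the first aTMS session. Count MADRS and quality-of-life weeks from that session in both arms. MoCA is already tied to treatment.

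**Cost.** Wording, plus a few extra ratings for the small number who do not requalify. Two limits remain. The week 1 comparison is made just after the early arm's treatment week, so it does not capture later response. Some regression to the mean stays in the pooled change whichever baseline is chosen.

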The proposed study is an open-label single-blinded study and will have the limitations of a lack of a control group in which patients will receive sham-operated magnetic stimulation of the brain and a control group to minimize the expectancy bias by raters. TMS is now a standard treatment for depression [62, 63]. Depression is a severe illness that could result not only in significant distress and economic burden for patients and society, but even suicide. It would be difficult to argue for a placebo-controlled arm in a pilot study of TMS with the availability of effective treatments for depression. In addition, we have both international [29, 64–66] and local evidence of the effectiveness of TMS in actual clinical settings to be able to meaningfully interpret the data from this open-label single-blinded study of TMS in treating depression. Nevertheless, proposing various groups of control without proper treatment of rTMS is unrealistic, particularly with the current recruitment capacity of a single research institute. Future large trial with multi-site collaboration may help to solve this issue.

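### Phase 2 allocation is attributed both to concealed permuted blocks and to the treating doctors, and the blinding claimed for patients and treating staff cannot be met

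*Protocol article*

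**What the plan says.** All references are to the protocol article.

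- **Allocation.** Under Randomization at phase 2, patients are stratified by MADRS improvement after the first course (three strata), and then "participants in each group will be randomized (in permuted blocks) to either L DLPFC or R DLPFC treatment". On who produces the sequence: "Randomization will be generated by study team members who are not involved in the treatment".
- **Assignment.** The next sentence is "Treatment assignment is determined by treating doctors".
- **Blinding.** The sentence after that is "Patients, their caregivers, nurse clinicians, and doctors who do the treatment and outcome assessments will be blinded to the randomization".
- **Arms.** Under Treatment at phase 2, patients receive "another 1 week of 5 Hz L DLPFC aTMS (same protocol as above) or aTMS consisting of right DLPFC at 1Hz". The coil sites are F3 for the left (Treatment at phase 1) and F4 for the right (Treatment at phase 2).
- **Time.** For the right arm: "1 Hz R DLPFC aTMS will take about 4 h a day". For the left 5 Hz course, Treatment at phase 1 says "Subsequent sessions are expected to last about 2 h each".
- **Rater.** Evaluation of clinical response at phase 2 assigns MADRS to a trained rater who does not know the arm.
- **Overall label.** Strengths and limitations says "The proposed study is an open-label single-blinded study".

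**The concern.** Two things go wrong in the same paragraph.

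First, the source of the arm is stated twice, with different answers. If the block sequence sets the arm, the treating doctors do not determine it. If the treating doctors determine it, the sequence has no force, and they cannot be blinded to a choice they made. Were doctors to influence the arm, those steered to a switch could differ systematically from those kept on the left. The comparison would then be confounded by indication, and no analysis could reliably undo that.

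Second, four groups are declared blinded to a contrast that most of them can see. If patient-rated phase 2 outcomes were presented as blinded, a difference in expectation between switching and having more of the same could be read as a treatment effect. The article itself stresses, under Strengths and limitations, how large placebo responses are in this field.

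The comparison at stake is the exploratory aim in Objectives. Sample size calculation says its results are meant to inform the power analysis of a later trial.

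**Working it through.** The plan gives no figure to reproduce here. The check has two parts: set the statements side by side, then ask from the plan's own stimulation parameters whether the arms can be told apart.

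**Part 1: consistency of the three statements**

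- (a) The sequence is generated by staff outside treatment, in stratified permuted blocks.
- (b) Treating doctors determine the assignment.
- (c) Treating doctors are blinded.

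Taken literally, (b) contradicts (a) and also contradicts (c). If (b) means only that treating doctors carry out the allocation, (a) survives. However, the doctors then know the arm, so (c) still fails unless it refers to the sequence alone.

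**Part 2: can the arms be distinguished?**

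Inputs for the left arm (Treatment at phase 1): 75 trains per session, 8 s on, 12 s between trains, 5 Hz, 4 sessions a day. Inputs for the right arm (Treatment at phase 2): 3000 pulses per session, 1 Hz, 4 sessions a day.

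Pulses = trains × seconds per train × Hz. Time = trains × (on + off).

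- Left: 75 × 8 × 5 = 3000 pulses, which matches the stated number. Time is 75 × 20 s = 1500 s = 25 min per session, and 4 × 25 = 100 min a day.
- Right: 3000 pulses at 1 Hz take at least 3000 s = 50 min per session, so at least 4 × 50 = 200 min (3.3 h) a day. This is a minimum because any gap between the 300 trains adds to it.

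The right-arm figure fits the stated 4 h or so a day. The left-arm 2 h is written per session, not per day. With sessions of 25 min it makes sense only as the length of the daily visit, which is an inference.

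Safety issues adds monitoring of at least 30 min after each session. If that applied separately after all four sessions, daily attendance would be 4 × (25 + 30) = 220 min on the left and at least 4 × (50 + 30) = 320 min on the right, a ratio of about 1.45 rather than 2.

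| Cue | Left arm | Right arm |
|---|---|---|
| Coil site | F3 | F4 |
| Pulse rate | 5 Hz | 1 Hz |
| Stimulation per day | 100 min | at least 200 min |
| Same as phase 1? | yes | no |

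The operator must place the coil on one side and set one frequency, so cannot be blinded. The patient has just had a week of left 5 Hz, feels which side is stimulated, and can notice the change in pulse rate and visit length. No masking of side or rate is described.

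**The case against.** Several points on the other side have force.

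- **The assignment sentence may be loose wording.** Strata, blocks and an uninvolved generator are all specified around it, so it may mean only that treating doctors carry out the allocation. A reader might infer that doctors choose the arm and that randomisation is undone. The text does not establish that; it establishes a contradiction. It still has to be corrected, because the words as they stand permit the harmful reading.
- **Blinding may refer to the sequence only.** That would ease the second problem, but not the conflict with doctors determining the assignment. Most readers will take the sentence as blinding to the arm.
- **MADRS has its own blinded rater.** A reader might infer from the blinding sentence that treating doctors rate outcomes and that MADRS is therefore unblinded. The sentence can equally mean doctors in either role, and the evaluation sections name a trained blinded rater for both phases. The stronger inference is not supported.
- **The limitation is partly disclosed.** The Abstract says single-blind, and Strengths and limitations concedes the lack of a sham arm and possible expectancy bias in raters. This does not repair the phase 2 sentence; it conflicts with it.
- **Duration is the weakest cue.** The per-session wording and the monitoring time both blur the twofold ratio. This stands, but side and pulse rate are enough without it.
- **Concealment mechanics belong in the full protocol.** Agreed. The point rests on statements that conflict, not on missing detail.

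**Conclusion.** The point holds as an internal contradiction on phase 2 allocation, together with a blinding claim that is impossible for operators and not credible for patients. It should be fixed.

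Its reach is limited to the exploratory left-versus-right comparison and the pilot estimates taken from it. A reader might infer that the primary result is compromised; the documents do not support that. Hypothesis and Sample size calculation put the powered aim on the overall-sample MADRS change to end of week 3, that is, one treatment week plus two weeks of follow-up, before phase 2 treatment. The article elsewhere names a four-week time point. Even there, the overall change is not a contrast between the phase 2 arms.

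No size in outcome units can be given. The documents do not say how many patients enter phase 2, how far doctors would influence the arm, or how strong expectancy is.

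Two assumptions apply. The quality-of-life questionnaire is taken to be completed by the patient. QIDS-16, which is self-rated, is named only under phase 1 and reaches phase 2 at most through the remark that assessment there is similar, so it counts only if it is collected in phase 2.

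**What to change.** 1. Delete the sentence that gives the assignment to treating doctors. State that the arm follows only the concealed stratified block sequence generated by staff outside treatment, and is revealed after phase 2 entry and the response stratum have been recorded.
2. Limit the blinding claim to the trained MADRS rater. Say that this person does not treat the patient being rated and is not told the arm.
3. Describe patients and treating staff as unblinded in phase 2, and bring this paragraph into line with Strengths and limitations.
4. Interpret patient-rated phase 2 outcomes (quality of life, and QIDS-16 if it is collected in phase 2) as unblinded.

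The cost is protocol wording and a local procedure. The uninvolved staff and the trained rater are already in the plan. The article says those staff generate the randomisation, not that they hold or release it, so that step may need to be set up. No visits, patients or treatments change.

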### Strengths and limitations

This trial has several strengths. The delayed start phase will decrease the likelihood of a significant placebo response by subjects who respond to increased attention in a clinical trial. The psychological response elicited by placebos is very specific depending on various factors such as the patient’s expectations, feelings, beliefs, volition, and hope for improvement [52, 53]. Growing placebo response is an important issue of antidepressant therapy for clinical trials involving patients with MDD [54–57]. A recent meta-analysis summarized from 61 large randomized clinical trials (RCTs) suggesting that there is a large placebo response for rTMS trial regardless of the modality of intervention [58]. In our trial, we designed a 1-week delay of treatment to possibly mitigate the placebo effect of active treatment by rTMS. However, it remains unclear whether this delayed-start phase may also reduce the anti-depressant effect of active treatment as some opinions exist that placebo response may be a component of therapeutic response to rTMS in MDD [58]. Patients will receive treatment as usual during the delayed week without coming to rTMS clinic. During the delayed phase, there is still weekly MADRS assessment and this will help patients maintain good adherence with the trial as the patients will keep informed about the study and establish a positive relationship and engagement with clinical staff.

We proposed a 2-week follow-up period after patients have been treated with compact 20 sessions of rTMS. Several open-label large-scale RCTs have shown that some patients with standard treatment of rTMS experienced a delayed response and required 4–6 weeks of stimulation before showing adequate response [12, 59–61]. Similarly, although the accelerated form of rTMS treatment with multiple sessions conducted daily may induce a rapid anti-depressant effect, there are still possibilities that some patients remain non-responding or poor-responding immediately after completion of prescribed sessions of rTMS. Therefore, 2 weeks follow-up period was proposed in this study to allow us to identify this specific group of patients with delayed responses.

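### Phase 2 assessment has two stated end points one week apart; under the earlier one, the week 6 response rate has no scheduled MADRS rating for phase 2 participants (weeks counted from treatment start)

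*Protocol article*

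**What the plan says.** All of these statements are in the Methods of the protocol article.

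- **Treatment at phase 2:** participants are "followed up with weekly assessments for 2 weeks after the end of the second round of aTMS".
- **Evaluation of clinical response at phase 2:** a blinded rater scores the MADRS weekly "until 2 weeks after the initiation of 2nd round of treatment". The same sentence opens by likening this to the phase 1 assessment.
- **Evaluation of clinical response at phase 1:** the rater "will assess mood each week, from baseline to 2 weeks after treatment". This section also fixes the outcome times: "The primary outcome is response rate, which are assessed at end of week 4 and week 6". It does not say from which day weeks 4 and 6 are counted.
- **Summary that closes the phase 2 evaluation section:** the primary outcome is a mean MADRS change at 4 weeks, counted from the start of treatment. The Hypothesis and the Sample size calculation use the end of week 3.

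**The concern.** The two phase 2 sentences describe the same follow-up but end it on different events. One counts from the end of round 2 and the other from its start. The sentence with the earlier end point is the one that governs MADRS ratings, so a rater who follows the evaluation section literally would stop a week before one who follows the treatment section.

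Two things depend on that week. The first is the week 6 response rate, which one section names as primary. The second is the exploratory comparison of repeated left-sided with switched right-sided stimulation, which has few post-treatment ratings as it is. A participant whose response appeared only in the last week would be recorded as a responder under one rule and a non-responder under the other.

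**Working it through.** **Inputs**

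- Round 1 lasts 1 week: "every weekday for 1 week. We will use a Magventure X100 TMS Therapy System" (Treatment at phase 1).
- Follow-up after round 1 lasts 2 weeks: "all subjects will then be followed up once a week for 2 weeks and subjects who achieve remission will exit the study" (Evaluation of clinical response at phase 1).
- Round 2 lasts 1 week: "Subjects who entered phase 2 will receive another 1 week of 5 Hz L DLPFC aTMS". The right-sided alternative also lasts 1 week (Treatment at phase 2).
- The delayed-start arm begins treatment 1 week after recruitment (Treatment at phase 1).
- Planned allocation is 20 early-start and 40 delayed-start (Sample size calculation).
- Assumption, not stated in the article: round 2 starts directly after the two follow-up weeks.

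**Formulas**

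Let d be the weeks between the zero of the clock and the start of active treatment.

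- Start of round 2 = d + 1 + 2
- End of round 2 = d + 1 + 2 + 1
- Last rating, end rule = (d + 4) + 2 = d + 6
- Last rating, initiation rule = (d + 3) + 2 = d + 5

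The difference is (d + 6) − (d + 5) = 1 week whatever d is, because it equals the length of round 2.

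**The plan's own figure**

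With d = 0 (clock from treatment start), the end rule gives 1 + 2 + 1 + 2 = 6. This reproduces the week 6 time point.

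**Results by clock and arm**

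| Clock | Arm | d | Last rating, end rule | Last rating, initiation rule | Week 6 rated under the initiation rule? |
|---|---|---|---|---|---|
| Treatment start | Early | 0 | 6 | 5 | No |
| Treatment start | Delayed | 0 | 6 | 5 | No |
| Randomisation | Early | 0 | 6 | 5 | No |
| Randomisation | Delayed | 1 | 7 | 6 | Yes |

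**Post-treatment ratings in phase 2 (d = 0)**

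Round 2 ends at week 4. The end rule gives post-treatment ratings at weeks 5 and 6, so two. The initiation rule gives week 5 only, so one.

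**Other stated time points (d = 0)**

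The end of week 3 (1 + 2) closes the phase 1 follow-up, and week 4 (1 + 2 + 1) closes round 2. Both fall before week 5, so both are rated under either rule.

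**The case against.** The strongest reply is that this is a slip of one word and the text nearly corrects it. The initiation sentence models itself on phase 1, where ratings continue for two weeks after treatment. The treatment section says the same for phase 2, and week 6 fits only that reading when counted from treatment start. This stands as evidence of what was meant. It does not remove the conflict, because the outlying sentence is the rating rule. The two figures are not shown to this review and may display the intended schedule, but the two sentences would still disagree.

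A second reply is that the week 6 visit does exist, since the treatment section schedules it. That is right. What is in doubt is whether the MADRS is rated there.

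Some stronger readings are tempting, and the documents do not support them:

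- **Week 6 is lost for every phase 2 participant.** This needs weeks counted from treatment start. The closing summary of the phase 2 evaluation section uses that clock, but the section naming week 6 states none. On a randomisation clock the delayed-start arm is still rated at week 6.
- **The trial loses its primary outcome.** Week 6 is one of several primary times that the article gives, and the end of week 3 and week 4 are observed either way.
- **The protocol itself says phase 2 needs two weeks to catch delayed responders.** The Discussion does say that a "2 weeks follow-up period was proposed in this study to allow us to identify this specific group of patients with delayed responses". But it is describing follow-up after 20 sessions, which is one round (4 a day × 5 weekdays), and it does not mention phase 2.
- **The two phase 2 arms have different windows.** Nothing in the article suggests this. The conflict applies equally to both.

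Finally, the left-versus-right comparison is labelled exploratory and meant to give pilot data, so the harm there is limited.

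**Conclusion.** The contradiction is real and does not depend on the clock: the two end points of phase 2 assessment are one week apart.

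Its consequence is conditional. With weeks counted from the start of active treatment and round 2 following directly on the two follow-up weeks, the initiation wording ends MADRS ratings at week 5. The week 6 response rate is then unscheduled for phase 2 participants in both start arms. With weeks counted from randomisation, the gap is confined to the early-start arm, 20 of the 60 planned. These are enrolment targets; the article does not give the number expected to enter phase 2. On either clock the exploratory comparison has one post-treatment week instead of two.

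Remitters who leave the study have no week 6 rating under either wording, so reconciling the sentences settles the schedule for those still in phase 2 and does not make week 6 observable in the whole sample. The point is worth correcting because an operative rating rule conflicts with a stated primary time point.

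**What to change.** Reconcile the two phase 2 sentences with each other and with the week 6 time point in the phase 1 evaluation section:

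1. In the phase 2 evaluation section, set the last MADRS rating at the visit two weeks after the end of round 2. This matches the treatment section, the stated likeness to phase 1, and week 6.
2. Where weeks 4 and 6 are named, state that weeks are counted from the start of active treatment.

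The cost is one corrected sentence and one added clause. No visit is added, because the treatment section already schedules weekly assessments up to that point.
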